### Sample size calculation

2.9

Based upon our experience in prior mapping studies approximately 30% of patients develop early post‐operative AF in the Erasmus MC,^13^ which is in correspondence with published literature.^14^

There is no data on the proposed novel electrophysiological parameters and biomarkers, and calculation of the sample size is therefore at present not possible. However, we used data obtained from a pilot study containing five patients with and five patients without AF. With a *P* value of 0.05 and a chosen power of 0.95 the required number is 135 per study group. An attrition rate of 10% increases this to 149 patients in each group. The required sample size for this study is therefore estimated at 447 patients. These calculations will be repeated after the first 50 patients in every group in order to adjust the sample size.

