**Results:**

The required sample size for this study is estimated at 447 patients. Up till now, 105 patients were included, of whom 36 have a history of AF.

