### Study population

2.2

Patients with structural heart disease scheduled for elective cardiac surgery are included. The study population consists of three study groups: patients with (longstanding) persistent AF (group 1), patients with paroxysmal AF (group 2) and patients without a history of AF (group 3) undergoing open‐chest cardiac surgery. In line with ESC guidelines, patients with documentation (ECG or ECG description) of self‐terminating AF episodes up to 7 days, or with AF episodes cardioverted within 7 days are classified as paroxysmal AF. Patients with documentation of AF episodes longer than 7 days or longer than a year are classified as persistent and longstanding persistent AF, respectively. Patients are recruited at the Department of Cardiothoracic Surgery at the Erasmus Medical Center, Rotterdam, The Netherlands. Prior to enrolling in the study, each patient is provided an oral and a written explanation of the study procedure. Written informed consent is obtained from all patients.

Prior to cardiac surgery, blood samples are taken from all patients for determination of proteostasis levels (Figure 2). Patient characteristics (eg, age, medical history, and cardiovascular risk factors) are obtained from the patient's file.

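### Minor arithmetic slip: 149 patients per group (447 in total) falls one per group short of delivering the required 135 after 10% attrition; dividing by 0.90 gives 150 and 450

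*Protocol article*

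**What the plan says.** Section 2.9 (Sample size calculation) builds the target in three steps.

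- The requirement: "With a *P* value of 0.05 and a chosen power of 0.95 the required number is 135 per study group".
- The attrition allowance: "An attrition rate of 10% increases this to 149 patients in each group".
- The total: "The required sample size for this study is therefore estimated at 447 patients".

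Section 2.2 confirms the multiplier: "The study population consists of three study groups". The Results paragraph of the abstract repeats the total: "The required sample size for this study is estimated at 447 patients".

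The same section describes its basis as thin: "we used data obtained from a pilot study containing five patients with and five patients without AF". It says that a proper calculation cannot yet be made, and it plans to redo the calculation once each group holds 50 patients. It does not say how the attrition allowance was applied.

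**The concern.** An attrition rate is normally read as the proportion of enrolled patients who do not contribute to the analysis. To end with n evaluable patients when a proportion d is lost, one enrols n/(1 − d). Multiplying by 1 + d instead adds d as a share of the evaluable number, which always gives too few.

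The step from 135 to 149 looks like the multiplication. If so, the stated target does not quite deliver the plan's own requirement at the plan's own attrition rate. What is at stake is the internal consistency of a number that section 2.9 and the abstract both present as required, and the method carried into the planned re-estimation. The study's ability to answer its questions is not at stake.

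**Working it through.** **Inputs, all from section 2.9 except the number of groups (section 2.2)**

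- Required per group: n = 135
- Attrition: d = 0.10
- Significance level 0.05 (sidedness not stated), power 0.95
- Groups: 3
- Stated result: 149 per group, 447 in total

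**1. Reproduce the stated figure**

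- n × (1 + d) = 135 × 1.10 = 148.5, rounded up to 149
- 149 × 3 = 447

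Both stated figures are matched exactly.

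**2. See what the stated figure delivers**

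- Per group: 149 × (1 − 0.10) = 134.1, against 135 required
- In total: 447 × 0.90 = 402.3, against 3 × 135 = 405 required
- Attrition that 149 covers in full: 1 − 135/149 = 14/149 = 9.4%

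**3. Apply the division**

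- n/(1 − d) = 135/0.90 = 150 per group
- 150 × 3 = 450 in total
- Check: 150 × 0.90 = 135
- Difference: 1 per group, 3 in total, 3/447 = 0.67%

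**4. Size the effect on power**

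The article gives no effect size or standard deviation, so 135 itself cannot be reproduced. Instead, take the effect that gives exactly 95% power at 135 per group and recompute power at 134.

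For a two-sided comparison of two means (normal approximation), the standardised difference is (1.960 + 1.645) × √(2/135) = 0.4388. Power at 134 is then Φ(0.4388 × √(134/2) − 1.960) = Φ(1.631) = 94.86%.

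| Test assumed | Power at 135 | Power at 134 |
|---|---|---|
| Two means, two-sided | 95.0% | 94.86% |
| Two means, one-sided | 95.0% | 94.87% |
| Three-group ANOVA (noncentral F) | 95.0% | 94.85% |

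The loss is about 0.15 percentage points whichever test is assumed.

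**5. Ask whether 149 could come from the division**

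It could if the unrounded requirement lay just above 134.0 and no higher than 134.1, with both steps rounded up: it would print as 135, and 134.1/0.90 = 149. That window is narrow, and the article presents 149 as what 135 becomes. On the printed figures 149 falls short under either formula, because 149 × 0.90 is less than 135.

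**The case against.** The strongest reply is that this makes no difference. One patient per group and 0.15 points of power are far smaller than the uncertainty of a requirement drawn from a ten-patient pilot. The article calls its total an estimate and plans to revise it. Recruitment points the same way: of the 105 patients reported in section 3, 16 had persistent or longstanding persistent AF (14 + 2), 20 had paroxysmal AF and 69 had no AF history (105 − 36). At those numbers, 149 or 150 is an academic distinction.

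That stands as an argument about size. It does not remove the inconsistency: the inputs and the output are printed side by side, and the output does not satisfy the inputs. Nor does provisional status settle the matter, since the article says the same calculations will be repeated, so the method of inflation still matters.

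It is also fair to object that the multiplication is inferred. It is the likely explanation, but it should be described as an inference.

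Two stronger readings are tempting. A reader might infer that 447 is a materially wrong sample size or that the study is underpowered because of this step; the 0.67% gap and the power figures above do not support that. A reader might also infer a larger shortfall from heavier loss over the five-year follow-up. The multiplication does err more at higher rates, but the article states only 10% and gives no basis for another figure.

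**Conclusion.** The point holds as a minor arithmetic slip in section 2.9, carried into the abstract. At 10% attrition, 149 per group leaves about 134 rather than 135; the division gives 150 per group and 450 in total. No conclusion of the study depends on the difference.

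This rests on three assumptions: that 135 is the number needed for analysis in each group, that 10% is the share of enrolled patients lost, and, for the power figure only, that 135 per group gives exactly 95% power under one of the tests tabulated above.

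**What to change.** Either of two text corrections is enough, made in both section 2.9 and the abstract so that they agree:

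- keep 149 per group and 447 in total, and state that this covers about 9.4% attrition; or
- restate the target as 135/(1 − 0.10) = 150 per group and 450 in total.

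In the planned re-estimation, print the formula and use n/(1 − d).

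The first option costs only wording. The second adds three patients to the target. Neither changes the design or the analysis.

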### Statistical analysis

2.10

Associations between proteostasis markers, electrical signals and clinical patient outcomes are calculated using multivariate logistic regression and cox regression models. Log rank tests compare patient groups with different stages of AF. Continuous and categorical electrophysiological parameters are compared with respectively ANOVA and chi‐square tests. For repeated biomarker measurements, joint modeling and mixed modeling analysis is used. ANOVA with Bonferroni adjustments corrects for analysis of multiple biomarkers.

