**Conclusion:**

The AFFIP study will elucidate whether electrophysiological and structural characteristics represent a novel diagnostic tool, the AF fingerprint, to predict onset and early progression of AF in cardiac surgery patients.

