## INTRODUCTION

1

Atrial fibrillation (AF) is the most common cardiac arrhythmia worldwide, and its incidence^1^ and associated medical health care costs^2^ continuously increase. Even though numerous predisposing factors for progression of AF have been identified, the exact pathophysiology remains incompletely understood and treatment of AF is associated with high recurrence rates. As disease progression from recurrent intermittent episodes to finally permanent AF is accompanied by a gradual increase in therapy failure, early recognition of AF is of prime importance. Persistence of AF is rooted in the presence of electropathology, which is defined as complex electrical conduction disorders caused by structural damage of atrial tissue. Therefore, early recognition of AF susceptibility in patients is necessary to halt electropathology and hence disease onset and progression. Although promising artificial intelligence applications are emerging,^3^ up till this day in clinical practice, AF is diagnosed with a surface electrocardiogram when a patient already suffers from AF. This rhythm registration cannot assess the degree of electropathology and thus the stage of AF which is essential for selection of the appropriate therapy. Hence, early recognition of AF and the start of effective treatment is seriously hampered. By characterizing electropathology, we aim to develop a novel diagnostic instrument to predict AF onset and early progression. We hypothesize that every patient has a unique biological and electrical signal profile that is influenced by age, gender and underlying heart disease. This bio‐electrical profile is deduced from the ratio abnormal/normal electrical signals in the atria by utilizing a unique high‐density atrial mapping approach and determination of proteostasis markers in tissue or blood samples related to structural damage. These outcomes are summarized in an AF Fingerprint.

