### Study objectives

2.1

The primary study objectives are to test the correlation between the AF fingerprint, revealing the degree of electropathology including for example, patterns of activation and signal morphology, proteostasis levels and atrial tissue characteristics, clinical characteristics and onset and progression of AF in patients undergoing open‐chest cardiac surgery.

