### Main study parameters and endpoints

2.8

Primary endpoint of the study is development or recurrence of AF. Secondary endpoints include implantation of an atrial pacemaker or implantable cardioverter defibrillator. Additional secondary endpoints are described in the Appendix S1. At present, no substudies are planned.

Deflections of the recorded atrial electrograms are detected semi‐automatically in custom‐made Python 3.6 software. In case of fractionated electrograms, the component with the steepest negative slope is taken as the local activation time (Figure 3). Electrograms with injury potentials and artifacts are excluded from analysis by consensus of two investigators. Signals are used to construct color‐coded activation, conduction block, break‐through wave, fractionation, and voltage maps (Figure 4). Furthermore, the relation between patterns of activation, incidence of breakthrough waves, fractionation, fibrillation intervals, conduction abnormalities, and voltage is studied and compared between the different atrial sites and atrial rhythms. Electrical changes as defined with the above‐mentioned electrical parameters will be correlated with the pre‐operative proteostasis levels, development of post‐operative AF, age, gender, and other clinical characteristics.

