**FIGURE 4 clc23370-fig-0004:**
[figure not shown]
Construction of the atrial fibrillation fingerprint (AFFIP). The left panel shows an example of an activation map during electrically induced atrial fibrillation (AF) of the left pulmonary vein area in a patient undergoing coronary artery bypass grafting without a history of AF. Isochrones are drawn at 5 ms, areas of conduction block (Δ local activation time [LAT] ≥ 12 ms) are indicated by black bars and the origin of peripheral waves by gray dots. The arrows indicate main activation direction. The corresponding fractionation map is displayed in the right panel and shows the different types of atrial potential morphologies: single potentials (SP, one deflection), short double potentials (sDP, two deflections less than 15 ms apart), long double potentials (lDP, two deflections 15 ms or more apart) and complex fractionated potentials (CFP, three or more deflections). The maps are used to determine the incidence of for example, fractionation and conduction block

The primary hypothesis is that the degree of electropathology will be increased in patients with a history of AF and patients whom develop post‐operative AF. Secondarily, we hypothesize that age, gender, underlying heart disease and other clinical characteristics impact the degree of electropathology.

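### The article promises a verdict on a predictive tool, but no stated analysis tests what the fingerprint adds to the clinical characteristics said to influence it

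*Protocol article*

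**What the plan says.** **The conclusion to be drawn.** The abstract's conclusion says the study will establish whether the measured characteristics "represent a novel diagnostic tool, the AF fingerprint, to predict onset and early progression of AF in cardiac surgery patients". The end of the introduction and the discussion repeat this in nearly the same terms.

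**The objective.** Section 2.1: "The primary study objectives are to test the correlation between the AF fingerprint", clinical characteristics, and AF onset and progression. These are listed in one chain, with none named as the reference for another.

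**The hypotheses.** In section 2.8 the primary hypothesis is a group difference: "the degree of electropathology will be increased in patients with a history of AF", and likewise in those who develop AF after surgery. The secondary hypothesis is that "age, gender, underlying heart disease and other clinical characteristics impact the degree of electropathology".

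**The analyses.** Section 2.8 correlates the electrical changes with marker levels, post-operative AF, "age, gender, and other clinical characteristics". Section 2.10 adds: "Associations between proteostasis markers, electrical signals and clinical patient outcomes are calculated using multivariate logistic regression and cox regression models". It then assigns ANOVA to continuous and chi-square tests to categorical electrophysiological parameters, with no covariates named.

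**What shapes the fingerprint.** The introduction hypothesises that each patient has a "unique biological and electrical signal profile that is influenced by age, gender and underlying heart disease". Section 2.2 takes age, medical history and cardiovascular risk factors from the patient's file, so they are known before surgery.

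**The concern.** A claim that something is a predictive tool is a claim about increment: it must predict better than what the clinician already has. Correlation with the outcome is a weaker property. A measurement influenced by age will correlate with any outcome that age also influences, even if it carries nothing else.

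The article names this common cause itself, then states tests that need not separate it from a contribution of the fingerprint. A positive answer to the objective as worded would therefore not settle the question that the conclusion is meant to answer.

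The parts of the fingerprint also differ in availability. Blood is drawn the day before surgery, whereas mapping and tissue need an open chest. Since the stated purpose is early recognition, the increment from each part is of interest, and no step is stated that would report it.

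**Working it through.** **1. The plan's own sample size.** Section 2.9 gives 135 per group and 10% attrition. 135 × 1.10 = 148.5, rounded up to 149; 3 × 149 = 447. Both stated figures reproduce. (Dividing by 0.90 gives 150 and 450, an immaterial difference.) Evaluable numbers are thus 135 in one group and 3 × 135 = 405 overall. No effect size is given, so the 135 itself cannot be checked.

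**2. Promise and tests side by side.**

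| Place | What is stated | Kind of evidence |
|---|---|---|
| Abstract, introduction, discussion | Verdict on a tool that predicts AF | Prediction |
| 2.1 | Correlation | Association |
| 2.8, primary hypothesis | More electropathology with AF | Group difference |
| 2.8, electrical parameters | Correlated with AF and, in the same list, age and gender | Association |
| 2.10, regression | Associations; multivariate, covariates not listed | Association, adjustment unknown |
| 2.10, ANOVA and chi-square | Comparison, no covariates named | Association, no adjustment stated |

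No row below the first is stated to compare prediction with and without the fingerprint.

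**3. What depends on the comparator.** A fingerprint with no effect of its own was simulated.

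- From the document: AF in 30% (section 2.9, early post-operative AF); n = 135 and 405; level 0.05.
- Assumed, because the document gives no values: odds ratio (OR) for AF of 1.5 to 2 per SD of age; correlation ρ between fingerprint and age of 0.3 to 0.7.
- Model: logit P(AF) = a + log(OR) × age, with age standardised and a set to give 30%; fingerprint = ρ × age + √(1 − ρ²) × noise.
- Unadjusted test: fingerprint by AF status. Adjusted test: fingerprint coefficient in a logistic model that contains age.

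| Test | n = 135 | n = 405 |
|---|---|---|
| Age not in the model | about 10-66% significant | about 19-98% significant |
| Age in the model | about 5% | about 5% |

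The low ends are OR 1.5 with ρ = 0.3; the high ends are OR 2 with ρ = 0.7. At OR 2 and ρ = 0.5 the unadjusted figure at n = 135 is about 39%. The mean AUC of the fingerprint alone is 0.53 to 0.63, although its added value is zero.

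**4. A second grid.** Table 1 gives age quartiles of 54 and 71. Under normality the SD is (71 − 54)/1.349 = 12.6 years. With assumed ORs of 1.25 to 2.0 per decade, ρ of 0.3 to 0.9 and n = 405, the fingerprint is significant in 12-100% of runs without age and 4-7% with it. At OR 1.5 and ρ = 0.5, mean AUC is 0.569 for the fingerprint, 0.638 for age and 0.641 for both. The gain over age is 0.641 − 0.638 = 0.003, and that is in-sample.

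**5. Whether a plain nested test would be enough.** Section 2.7 lists 19 markers. In one study group, 0.30 × 135 = 40.5, about 41 events. Adding 19 markers with no effect to four clinical variables gave likelihood-ratio rejection in about 11-14% of runs and an in-sample AUC gain of 0.12 at n = 135. At n = 405 the figures were 7% and 0.05. An uncorrected nested comparison would therefore itself favour an uninformative fingerprint too often.

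**The case against.** The stronger reading is that the plan never relates the fingerprint to clinical characteristics, so that one which merely carries age would pass. A reader might infer this, but the document does not support it. The introduction plans to compare fingerprints across age groups, gender and heart disease. Section 2.1 includes clinical characteristics, section 2.8 correlates electrical parameters with them, and section 2.10 calls its regressions multivariate. If age is a covariate, an age-only fingerprint is significant at about the nominal 5%. Hence it could pass if age is omitted; that it would pass is not established. The large percentages in the working describe a model without age, which the regression sentence neither states nor excludes.

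It can also be said that covariate lists and performance measures belong in a full protocol or analysis plan. That is right, and their absence from an article is not the point here. The objective and the conclusion it is to support are both stated in the article, and they call for different evidence. A significant adjusted coefficient would still not show how much prediction improves.

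The abstract and discussion also describe a softer aim: characterising electropathology so that an instrument can be developed. This eases the mismatch, but the promised verdict on a predictive tool remains.

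Finally, nothing prevents separate estimates for blood and invasive measurements, so the plan cannot be said to be unable to distinguish them. It only states no step that would.

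**Conclusion.** The point holds as a mismatch between the stated conclusion (prediction) and the stated objective and analyses (correlation, association, group comparison). It matters because the article itself says age, gender and heart disease influence the fingerprint. It applies most directly to the ANOVA and chi-square comparisons, where no adjustment is stated; for the regressions it is conditional on what the covariates are.

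The size is conditional too: about 10-66% (n = 135) or 19-98% (n = 405) false support for an age-only fingerprint if age is left out, and about 5% if it is included. The width of these ranges shows that they follow from the assumed odds ratios and correlations. They show that the choice of comparator can decide the answer; they do not predict this study's error rate. The change should be made, but the point does not invalidate the data being collected.

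**What to change.** In sections 2.1 and 2.10, base the predictive conclusion on nested models fitted in the same patients:

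- (a) clinical characteristics from the file: age, gender, underlying heart disease, cardiovascular risk factors;
- (b) model (a) plus the pre-operative blood markers;
- (c) model (b) plus the mapping and tissue parameters.

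Reduce each added block to a small pre-specified or penalised score, rather than entering all markers. For (b) versus (a) and (c) versus (b), report the test of the increment and the optimism-corrected (bootstrap or cross-validated) change in AUC or C-index with its confidence interval. Conclude that the fingerprint is a predictive tool only if it improves on (a); otherwise limit the conclusion to association.

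This needs no new patients or measurements, and 105 of the 447 planned patients had been included at the time of the article. The cost is more than wording: the scores must be fixed in advance, the optimism correction adds analysis work, and the hurdle is harder than a plain correlation.

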**FIGURE 2 clc23370-fig-0002:**
[figure not shown]
Time course of the atrial fibrillation fingerprinting (AFFIP) study. A baseline blood sample (red bar) is obtained from all patients 1 day prior to surgery. During surgery, the study procedure (blue bar, epicardial mapping) is performed, followed by post‐operative continuous rhythm monitoring (orange bar). Patients are consulted by phone at 6 months, 12 months, and yearly up to 5 years after surgery for detection of late post‐operative atrial fibrillation (AF) (green bars)

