### Intra‐operative mapping procedure

2.5

Epicardial mapping is performed during surgery. Patients are under full anesthesia and vital signs are monitored continuously throughout the procedure. Epicardial unipolar electrograms are recorded using a custom‐made multi‐site electrode array. Recordings are made at nine consecutive sites (right atrium 1‐4, Bachmann's bundle, right and left pulmonary vein, and left atrium 1‐2), following a predefined mapping scheme (Figure 3) during SR (nine sites, 5 seconds/site), during pacing maneuvers for inducing AF (one site, Bachmann's bundle), and in AF (nine sites, 10 seconds/site). Pacing is performed with atrial fixed rate pacing directly from the electrode or with a standard temporary pacemaker wire. If AF sustains at the end of the mapping procedure, SR is restored with 5‐10 J electrical cardioversion.

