**FIGURE 3 clc23370-fig-0003:**
[figure not shown]
Epicardial mapping to retrieve unipolar atrial electrograms. With the use of a 192 electrode arrays, the left atrium (LA), right atrium (RA), pulmonary vein (PV) area, and Bachmann's bundle (BB) are mapped following this predefined mapping scheme. Unipolar atrial electrograms are collected during sinus rhythm (SR), pacing maneuvers (P), and (electrically induced) atrial fibrillation (AF). Morphology of atrial potentials are subdivided into four categories: single potentials (one deflection), short double potentials (two deflections less than 15 ms apart), long double potentials (two deflections 15 ms or more apart), and complex fractionated potentials (three or more deflections). ICV, inferior caval vein; LAA, left atrial appendage; PVL, left pulmonary vein area; PVR, right pulmonary vein area; RAA, right atrial appendage; SCV, superior caval vein

After introduction of the extra corporal circulation into the right atrium via the right atrial appendage (RAA) a tissue sample (approximately 10 × 10mm) is obtained from the incision site in all patients. In patients undergoing mitral valve surgery, the left atrial appendage (LAA) is also incised and a small tissue sample is excised. In patients undergoing surgical pulmonary vein isolation, a left sided procedure in patients with AF which includes amputation of the LAA, the LAA tissue is also studied.

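### Mapping parameters are to be compared between sites and rhythms within the same patient, but the only tests named for them ignore that pairing, and mixed models are assigned to biomarkers for which a single blood sample is described

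*Protocol article*

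**What the plan says.** All references are to the protocol article.

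- **Data structure.** Section 2.5: "Recordings are made at nine consecutive sites", in sinus rhythm and again in AF, plus pacing at one site. The Figure 3 legend gives the array size: "With the use of a 192 electrode arrays".
- **Planned comparisons.** Section 2.8 states that the relation between the mapping parameters "is studied and compared between the different atrial sites and atrial rhythms". The same section gives the primary hypothesis: "The primary hypothesis is that the degree of electropathology will be increased in patients with a history of AF" and in those who develop post-operative AF.
- **Tests for mapping parameters.** Section 2.10: "Continuous and categorical electrophysiological parameters are compared with respectively ANOVA" and chi-square tests. It names no repeated-measures, paired, mixed or cluster-adjusted form.
- **Where mixed models appear.** Section 2.10: "For repeated biomarker measurements, joint modeling and mixed modeling analysis is used".
- **Biomarker sampling.** Figure 2 legend: "A baseline blood sample (red bar) is obtained from all patients 1 day prior to surgery". No later blood sample is described. Right atrial appendage (RAA) tissue is taken at surgery in all patients. In mitral valve surgery "the left atrial appendage (LAA) is also incised and a small tissue sample is excised", and LAA tissue is also studied after surgical pulmonary vein isolation (section 2.5).
- **Clinical outcomes.** Section 2.10 assigns their associations with markers and electrical signals to logistic and Cox regression.

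**The concern.** The methods look assigned the wrong way round. The mapping data are repeated within patient by design and will be compared across sites and rhythms, yet they receive tests that assume independent observations. The methods that handle within-patient correlation go to biomarkers, for which the described schedule shows no repeated blood measurement. A joint model needs a marker followed over time, and none is described.

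Two different consequences are possible:

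- **Between sites or rhythms.** Ignoring the patient leaves the between-patient variance in the error term. The test becomes conservative and loses power.
- **Between AF groups.** If several rows per patient were treated as independent, the standard error would be too small and the type I error too large. This depends on the unit of analysis, which the article does not state.

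**Working it through.** **Inputs from the article.** Nine sites per rhythm (section 2.5); three study groups (section 2.2); alpha 0.05 and 135 patients per group before attrition (section 2.9), so 3 × 135 = 405.

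**The plan's own figure.** Section 2.9 gives 135, then 149 after 10% attrition (135 × 1.1 = 148.5), then 3 × 149 = 447. The attrition and total steps reproduce. The 135 cannot be reproduced, because no effect size or SD is given. It serves here only as a sample size.

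**Assumptions.** The article gives no within-patient correlation. ICC values of 0.05 to 0.5 are assumed, with equal correlation between all sites, total variance 1 and one value per patient and site. The power example assumes one site shifted by d = 0.25 SD.

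**1. Between-site comparison, no true difference.** The within-patient F test uses error variance 1 − ICC. ANOVA without a patient term uses error variance of about 1, so its F is about (1 − ICC) times the within-patient F. Simulated rejection rates at nominal 5%, with 405 patients:

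| ICC | ANOVA without patient term | Repeated-measures ANOVA |
|---|---|---|
| 0.1 | 0.030 | 0.054 |
| 0.3 | 0.005 | 0.045 |
| 0.5 | below 0.001 | 0.052 |

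**2. Between-site comparison, power at ICC 0.5.** The noncentrality of the within-patient test is λ = n·d²·(1 − 1/9)/(1 − ICC).

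- n = 135: λ = 135 × 0.0625 × 0.889/0.5 = 15.0. The 5% critical value is about 1.95 (8 and 1,072 df), and power is about 79% to 80%. Without the patient term, the within-patient F would have to exceed about 1.95/0.5 = 3.9, and power is about 17% to 18%.
- n = 405: λ = 45.0. Power is about 100% within-patient and about 95% without the patient term.

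The loss is therefore large in a comparison confined to one study group and small in this example when all groups are pooled.

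**3. AF-group comparison if nine site rows were treated as independent.** The design effect is 1 + (9 − 1) × ICC. For the three-group test (2 df, critical value 5.99), the true type I error is P(χ²₂ > 5.99/design effect) = exp(−2.996/design effect).

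| ICC | Design effect | True SE / naive SE | Type I error |
|---|---|---|---|
| 0.05 | 1.4 | 1.18 | 12% |
| 0.1 | 1.8 | 1.34 | 19% |
| 0.3 | 3.4 | 1.84 | 41% |
| 0.5 | 5.0 | 2.24 | 55% |

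Simulated ANOVA at ICC 0.1, 0.3 and 0.5 gave 20%, 41% and 55%. Chi-square on nine binary site rows (prevalence 0.2 assumed) gave 19%, 41% and 55%.

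**4. AF-group comparison with one mean per patient.** Simulated type I error was 5.8%, 5.1% and 5.1% at the same three ICC values. Ordinary ANOVA is valid here.

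**The case against.** The strongest reply is that a reader might infer from all this that the standard errors of the main analysis are wrong, and the article does not support that.

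- The primary endpoint is development or recurrence of AF, one outcome per patient, and it goes to logistic and Cox regression. Nothing here touches those models.
- The primary hypothesis compares patients. The introduction describes the profile as a ratio of abnormal to normal signals, which fits one value per patient, and the sample size counts patients. No sentence says that sites or electrograms enter as independent rows.
- Repeated-measures ANOVA is also an ANOVA, and a condensed article may leave its form and the unit of analysis to the full protocol or SAP.
- For the comparisons that are plainly within-patient, the error with one value per patient and site is conservative.
- Some patients give both RAA and LAA tissue, so mixed models for biomarkers may have a use.

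Most of this stands. It removes any claim about the primary endpoint, makes the inflated type I error conditional, and rules out deleting the biomarker models outright. It does not remove the mismatch. The article goes beyond leaving the method open: it names tests for these parameters, and in the next sentence ties the methods for repeated data to biomarkers only. The usual chi-square test has no repeated-measures form, so a generous reading of the word ANOVA does not help the categorical parameters.

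**Conclusion.** The point holds in a limited form. The tests named in section 2.10 do not fit the site and rhythm comparisons planned in section 2.8. With one value per patient and site they are conservative and lose power. At an assumed ICC of 0.5 and a shift of 0.25 SD at one site, power is about 18% against 79% with 135 patients, and 95% against 100% with 405.

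The AF-group comparisons are at risk only if sites or electrograms are pooled as independent rows. Type I error would then be about 19%, 41% and 55% at assumed ICC 0.1, 0.3 and 0.5 for nine sites and three groups. The article neither states nor excludes that, and with one summary value per patient these tests are valid.

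Every size given rests on an ICC that the article does not supply. The conservative direction rests on one value per patient and site with equal correlation between sites; electrogram-level rows were not worked through for site comparisons.

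**What to change.** Change section 2.10 as follows.

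1. **Site and rhythm comparisons.** Use linear mixed models for continuous parameters and generalised linear mixed models for categorical ones. Include fixed effects for AF group, site and rhythm and a random patient effect, and add a random effect for site within patient where electrogram-level data are analysed.
2. **AF-group comparisons.** State that the patient is the unit of inference, either through the same models or by reducing each parameter to one summary value per patient before ANOVA or chi-square.
3. **Biomarkers.** Say which measurements are repeated. Keep joint modelling only if a marker is measured serially. Otherwise enter the baseline blood markers as covariates in the logistic and Cox models, and use mixed models for paired RAA and LAA tissue markers.

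The cost is a wording change and slightly more analysis work, with no new data. Confidence intervals will be wider for any group comparison that would otherwise have pooled rows. With 105 of 447 patients enrolled as of March 20, 2020, the article left room to make the change before the main analysis.
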